## Abstract

**Introduction:**

There is a high risk of stroke occurrence and recurrence in patients with intracranial atherosclerotic stenosis (ICAS) despite aggressive medical therapy. Evolocumab is a monoclonal antibody which can inhibit proprotein convertase subtilisin-kexin type 9 (PCSK9) and effectively reduce the level of low-density lipoprotein cholesterol. We hypothesize that evolocumab added to statin therapy (EAST) can stabilize intracranial plaques in patients with symptomatic ICAS.

**Methods and analysis:**

This is a prospective, randomized, open-label, blinded end-point study, which will assess the efficacy and safety of evolocumab in patients with symptomatic ICAS. Eighty patients who suffer a stroke/transient ischemic attack (TIA) caused by ICAS recently will be randomly allocated in a 1:1 ratio to the evolocumab plus statin treatment group or the statin treatment group. High resolution vessel wall magnetic resonance imaging (HR-vwMRI) will be performed at recruitment and after 6 months and 12 months. The primary outcome is changes in plaque characteristics assessed by HR-vwMRI at 6th month and 12th month after treatment. Cognitive and neurological function will also be evaluated at recruitment and follow-up. This trial is being conducted at the first affiliated hospital of Nanjing medical university, China.

**Ethics and dissemination:**

All participants will sign written informed consents. Peer-reviewed articles will be published to disseminate study outcomes.

**Clinical trial registration:**

ClinicalTrials.gov, identifier: NCT05741086.

## Introduction

1

Intracranial atherosclerosis stenosis (ICAS) is one of the important causes of ischemic stroke occurrence and recurrence worldwide and is especially common in Asian (1, 2). It accounts for 30–50% of strokes in Asian, but only 5–10% in the West (3, 4). Aggressive medical management (e.g., high intensity statin therapy to reduce low-density lipoprotein (LDL) cholesterol <1.8 mmol/L) is superior to the percutaneous transluminal angioplasty and stenting for symptomatic ICAS in the SAMMPRIS study. However, around one in five patients still experienced stroke recurrence or death during 3-year follow-up in the aggressive medical treatment group (5).

As a fully human monoclonal antibody and a member of proprotein convertase subtilisin-kexin type 9 (PCSK9) inhibitors, evolocumab has the potential to decrease LDL cholesterol levels by around 60%. The FOURIER study showed that evolocumab decreased cardiovascular events (i.e., cardiovascular death, myocardial infarction, and stroke), in patients with atherosclerotic cardiovascular disease during 2.2 years follow-up (6). It’s still largely unknown whether evolocumab could affect the evolution of ICAS and reduce ischemic events in patients with stroke.

We thus designed this prospective, randomized, open-label, blinded end-point study to evaluate the effects of evolocumab added to statin therapy (EAST) in patients with stroke/transient ischemic attack (TIA) caused by ICAS. Eighty patients will be enrolled and assigned into two arms with or without evolocumab. Changes in plaque characteristics on high resolution vessel wall magnetic resonance imaging (HR-vwMRI), neurological function and cognitive function will be evaluated and analyzed between groups over a period of 1 year follow-up.

## Materials and methods

2

### Study design

2.1

This is a prospective, randomized, open-label, and blinded endpoint assessment study. We will recruit 80 patients who have recently suffered a stroke/transient ischemic attack (TIA) due to ICAS. The inclusion and exclusion criteria are shown in Tables 1, 2, respectively. Patients will be allocated in a 1:1 ratio to the evolocumab plus statin treatment arm or the statin alone treatment arm. Evolocumab (150 mg) will be injected subcutaneously every 2 weeks for 12 months. Both arms will receive statins for 12 months, including atorvastatin 20–80 mg or rosuvastatin 10–20 mg. According to current guideline and the standards in SAMMPRIS study, optimal medical management with aggressive control of the risk factors will be provided to all patients, such as proper application of antiplatelet, antihypertensive, and antidiabetic drugs. HR-vwMRI will be performed at baseline and at 6th and 12th month after recruitment. Blood test will be conducted at baseline and at 1st, 3rd, 6th, and 12th month after recruitment. National Institute of Health Stroke Scale (NIHSS), modified Rankin Scale (mRS), Barthel index, Mini-Mental State Examination (MMSE), and Montreal Cognitive Assessment (MoCA) will be evaluated at baseline and at 3rd, 6th, and 12th month post-recruitment. This study was approved by the ethics board of the first affiliated hospital of Nanjing Medical University. Written informed consents will be obtained. The flow chart of this study is shown in Figure 1.

**Table 1 tab1:** Inclusion criteria.

1. Age ≥30 years and ≤75 years
2. TIA or acute ischemic stroke that occurred within 6 weeks prior to randomization
3. Modified Rankin score of ≤4
4. TIA or acute ischemic stroke attributed to a 50 to 99% stenosis of a major intracranial artery [internal carotid artery (ICA), vertebral artery (VA), basilar artery (BA) and the M1 segment of middle cerebral artery (MCA)]. The diagnostic evaluation for ICAS at each site is confirmed by the local investigator, using high resolution MR
5. To increase the likelihood that the symptomatic intracranial stenosis is atherosclerotic, patients aged 30–49 years are required to meet at least one additional criteria (i–vi) below:
o Insulin dependent diabetes for at least 15 years
o At least 2 of the following atherosclerotic risk factors: hypertension [blood pressure (BP) ≥140/90 or on antihypertensive therapy]; dyslipidemia [LDL ≥130 mg/dL or high density lipoprotein (HDL) <40 mg/dL or fasting triglycerides ≥150 mg/dL or on lipid lowering therapy]; smoking; non-insulin dependent diabetes or insulin dependent diabetes of less than 15 years duration; family history of any of the following: myocardial infarction, coronary artery bypass, coronary angioplasty or stenting, stroke, carotid endarterectomy or stenting, peripheral vascular surgery in parent or sibling who was <55 years of age for men or <65 for women at the time of the event
o History of any of the following: myocardial infarction, coronary artery bypass, coronary angioplasty or stenting, carotid endarterectomy or stenting, or peripheral vascular surgery for atherosclerotic disease
o Any stenosis of an extracranial carotid or vertebral artery, another intracranial artery, subclavian artery, coronary artery, iliac or femoral artery, other lower or upper extremity artery, mesenteric artery, or renal artery that was documented by non-invasive vascular imaging or catheter angiography and is considered atherosclerotic
o Aortic arch atheroma documented by non-invasive vascular imaging or catheter angiography
o Any aortic aneurysm documented by non-invasive vascular imaging or catheter angiography that is considered atherosclerotic
6. Patient agrees with follow-up visits and is available by phone
7. Patient understands the purpose and requirements of the study, can make him/herself understood, and has signed informed consent

**Table 2 tab2:** Exclusion criteria.

1. Previous treatment of target intracranial lesion with a stent, angioplasty, or other mechanical devices (e.g., mechanical thrombectomy, coil embolization)
2. Plan to perform angioplasty, stenting, coiling, thrombectomy, endarterectomy or aneurysmal coil embolization for target vessels/plaques. In case that patients who receive surgeries during follow-up, they will still be followed up for 1 year
3. Intracranial tumor (except meningioma) or any intracranial vascular malformation
4. History of any intracranial hemorrhage (parenchymal, subarachnoid, subdural, epidural)
5. Intracranial arterial stenosis due to arterial dissection; moyamoya disease; any known vasculitic disease; viral vasculopathy; neurosyphilis; any other intracranial infection; any intracranial stenosis associated with cerebral spinal fluid pleocytosis; radiation induced vasculopathy; fibromuscular dysplasia; sickle cell disease; neurofibromatosis; benign angiopathy of central nervous system; postpartum angiopathy; suspected vasospastic process; reversible cerebral vasoconstriction syndrome (RCVS); suspected recanalized embolus
6. Presence of any of the following unequivocal cardiac sources of embolism: chronic or paroxysmal atrial fibrillation, mitral stenosis, mechanical valve, endocarditis, intracardiac clot or vegetation, myocardial infarction within 3 months, dilated cardiomyopathy, left atrial spontaneous echo contrast, ejection fraction less than 30%
7. Use of cholesteryl ester transfer protein (CETP) inhibition treatment, mipomersen, or lomitapide within 12 months prior to randomization. Fenofibrate therapy must be stable for at least 6 weeks prior to final screening at a dose that is appropriate for the duration of the study in the judgment of the investigator. Other fibrate therapy (and derivatives) are prohibited
8. Prior use of PCSK9 inhibition treatment before this recruitment
9. Known allergy or contraindication to aspirin, clopidogrel, evolocumab or statin
10. Active peptic ulcer disease, major systemic hemorrhage within 30 days, active bleeding diathesis, platelets <100,000, hematocrit <30, international normalized ratio (INR) >1.5, clotting factor abnormality that increases the risk of bleeding, current alcohol or substance abuse, uncontrolled severe hypertension (systolic pressure >180 mm Hg or diastolic pressure >115 mm Hg), severe liver impairment [aspartate transaminase (AST) or alanine transaminase (ALT) >3× normal, cirrhosis], creatine kinase >5 times the upper limit of normal (ULN) at final screening, severe renal dysfunction, defined as an estimated glomerular filtration rate (eGFR) <20 mL/min/1.73 square meter at final screening
11. Major surgery (including open femoral, aortic, cardiac or carotid surgery) within previous 30 days or planned in the 1 year after enrollment
12. Dementia or psychiatric problem that prevents the patient from relevant evaluation or follow-up reliably
13. Co-morbid conditions that may limit survival to less than 1 year
14. Currently breastfeeding, pregnancy, planning to become pregnant and unwilling to use contraception for the duration of this study
15. Enrollment in another study that would conflict with the current study

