### Study outcomes

3.1

Primary endpoints:

1) Changes in plaque enhancement.

A reduction of ≥ 1 grading in plaque enhancement after 12 months’ treatment was regarded as relief of plaque enhancement. For example, a patient’s plaque enhancement reduces to grade 1 or even 0 after 12 months’ treatment, compared to grade 2 at the time of enrollment.

2) Changes in degree of stenosis.3) Changes in plaque enhancement ratio.4) Changes in plaque burden.5) Changes in hypoperfusion volume.6) T1 hyperintensity.

We define three types of T1 hyperintensity changes at 12 month after recruitment: type A, no changes before and after treatment; type B, disappearance of T1 heperintensity; type C, new T1 hyperintensity.

7) Changes in remodeling index (RI) of the plaque.

Secondary endpoints:

1) Recurrent stroke (ischemic or hemorrhagic) or death during follow-up.2) Changes in LDL-cholesterol levels.3) Changes in NIHSS/Barthel index/mRS score.4) Changes in MoCA/MMSE score.

All changes above before and after treatment in each arm will be calculated and compared between arms.

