Nowadays, the treatment of ICAS is mainly composed of antiplatelet therapy, lipid-lowering strategies, the modification of risk factors and interventional procedures (15). Statins are the preferred treatment option for lowering LDL-C (16). It has been observed that intensive statin therapy can stabilize symptomatic intracranial atherosclerotic plaques, as evidenced by a reduction in enhancement and stenosis on sequential HR-MRI assessments. In addition, greater reductions in LDL levels are associated with a more pronounced decrease in plaque enhancement (17). However, more than a third of these patients demonstrated either no improvement or a worsening of plaque enhancement and stenosis after high-dose statin therapy, suggesting a lack of or minimal responsiveness to statins (17). This is consistent with earlier findings regarding the progression of ICAS in patients treated with statins (3, 18). Meanwhile, there is an association between high-intensity statin therapy and increased side effects, including myalgia and liver dysfunction, which can result in inadequate treatment adherence. Endovascular treatments such as stenting may be a promising treatment method for ICAS. Nevertheless, the CASSISS study found that there was no significant difference between stenting combined with drug therapy and drug therapy alone in preventing stroke or death (19). As a member of PCSK9 inhibitor family, evolocumab significantly reduces LDL cholesterol levels, and associated with greater plaque regression and stabilization by optical coherence tomography measures of plaque composition (20), reducing the risk of cardiovascular events (6). Therefore, it is plausible that evolocumab added to statin therapy (EAST) could also stabilize intracranial plaques in stroke/TIA patients with ICAS.

In this study, symptomatic ICAS patients will be randomized into the arm of evolocumab plus statin or the arm of statin alone. The evolution of these plaques will be monitored through sequential HR-vwMRI scans at 6-months and 12-months after enrollment. Future multicenter studies with a large sample size are needed to further investigate the efficacy of this “EAST” strategy in symptomatic ICAS.

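### Change endpoints are compared by unadjusted two-sample tests, although baseline may fall anywhere in the six weeks after the event and in patients with or without prior statin use

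*Protocol article*

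**What the plan says.** **Entry window.** Table 1 (section 2.1), criterion 2, requires a "TIA or acute ischemic stroke that occurred within 6 weeks prior to randomization". It sets an upper limit only. Baseline imaging, blood tests and rating scales are done at recruitment.

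**Prior lipid treatment.** No criterion excludes or limits prior statin use. Criterion 5, which applies to patients aged 30–49, counts existing treatment towards the dyslipidaemia risk factor: "fasting triglycerides ≥150 mg/dL or on lipid lowering therapy". Table 2 bars prior PCSK9 inhibitors and sets a stability rule for one other lipid drug: "Fenofibrate therapy must be stable for at least 6 weeks prior to final screening". In the trial, "Both arms will receive statins for 12 months, including atorvastatin 20–80 mg or rosuvastatin 10–20 mg".

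**Size and allocation.** "We will recruit 80 patients who have recently suffered a stroke/transient ischemic attack (TIA) due to ICAS", and "Patients will be allocated in a 1:1 ratio to the evolocumab plus statin treatment arm or the statin alone treatment arm".

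**Endpoints.** Section 3.1 lists seven primary endpoints, all changes in imaging features, and secondary changes in LDL, NIHSS, Barthel index, mRS, MoCA and MMSE. It adds: "All changes above before and after treatment in each arm will be calculated and compared between arms".

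**Analysis.** Section 3.3 names Fisher's exact or Pearson's chi-squared test for categorical data and Student's t or Mann–Whitney for continuous data. A model appears only for stroke or death (Cox).

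**Link to statins.** The Discussion reports that intensive statin therapy lowers enhancement and stenosis on serial imaging, and that "greater reductions in LDL levels are associated with a more pronounced decrease in plaque enhancement".

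**The concern.** A change score depends on where the patient stands at baseline. One patient may be scanned days after the event while starting a first statin. Another may be scanned at six weeks after years on a statin. On the Discussion's own account of what statins do, the first plausibly has more statin-driven change still to come, in either arm.

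Similarly, change in NIHSS, Barthel index and mRS depends on how much recovery came before baseline, and on whether the event was a TIA or a stroke. The baseline value of the outcome does not carry all of this: two plaques with the same enhancement grade, one untreated and one long treated, may be expected to evolve differently.

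An unadjusted test leaves this variation in the error term and cannot correct for a chance difference between arms. At stake are precision in a small trial and how far a borderline result can be trusted.

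**Working it through.** **Inputs from the article:** 80 patients, 1:1, so 40 per arm; change endpoints; unadjusted tests; significance at 0.05 (two-sided assumed). The article gives no effect size, SD or power for the 80, so there is no planned figure to reproduce. For orientation, at 80% power 40 per arm detects (1.960 + 0.842) × √(2/40) = 0.626 SD.

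**Assumptions, not in the article:** a share p = 0.3–0.5 is statin-naive at baseline, and mean change differs by g = 0.4–0.8 within-group SD between naive and treated patients.

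**1. Variance explained** = p(1−p)g² / [1 + p(1−p)g²].
- Low end (p = 0.3, g = 0.4): 0.0336 / 1.0336 = 3.3%; × 80 = 2.6 patients.
- High end (p = 0.5, g = 0.8): 0.16 / 1.16 = 13.8%; × 80 = 11.0 patients.

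**2. Detectable difference and power, unadjusted, p = 0.5.** The SD is inflated by √(1 + 0.25g²), which is √1.04 = 1.020 at g = 0.4 and √1.16 = 1.077 at g = 0.8.
- Detectable difference: 0.626 × 1.020 = 0.639 and 0.626 × 1.077 = 0.675.
- Power at a true 0.6265 SD: Φ(0.6265 / (0.2236 × 1.020) − 1.960) = 78%, and with 1.077, 74%. Full adjustment holds it near 80%.
- Beyond the assumed range, at g = 1, the unadjusted power is 71%. In a simulation of 4,000 trials a model with the factor included gave about 78%.

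**3. Chance imbalance in the naive share, without stratification.** Two calculations are shown: each arm as Binomial(40, p), and the overall share held fixed (hypergeometric).

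| Difference between arms | Binomial, p = 0.3 / 0.5 | Fixed share, p = 0.3 / 0.5 |
|---|---|---|
| ≥ 15 points | 0.179 / 0.219 | 0.222 / 0.263 |
| ≥ 20 points | 0.067 / 0.093 | 0.087 / 0.117 |

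**4. Shift from a 20-point imbalance** (24 against 16 of 40, p = 0.5): 0.2g divided by the total SD.
- g = 0.4: 0.08 / 1.020 = 0.078 SD.
- g = 0.8: 0.16 / 1.077 = 0.149 SD.

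**5. False-positive rate of the t-test given the imbalance** (simulation, 200,000 runs, no drug effect).

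| Split of naive patients | g = 0.4 | g = 0.8 |
|---|---|---|
| 24 v 16 | 6.0% | 8.3% |
| 22 v 18 | 4.9% | 4.7% |
| 20 v 20 | 4.5% | 3.5% |

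A shortcut that adds the shift to a unit-variance test statistic gives 6.4% and 10.2% for the 24 v 16 split. It overstates the rate: once the split is fixed, the factor no longer contributes to sampling variation, but the test's standard error still contains it.

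**6. Unconditional false-positive rate.** Over random allocations, with gaps from 0 to 2 SD, the unadjusted test rejected in 4.3–5.1% of 4,000 simulated trials per setting. It is valid on average.

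Time since the event and event type are not in these figures. The article gives nothing from which to size them.

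**The case against.** **Randomisation protects the comparison.** A reader might infer that mixed baselines bias the arm difference. They do not. Both factors are balanced in expectation, the unconditional error stays at about 4–5%, and the same test is conservative when the arms happen to balance. What remains is lost precision and exposure to an unlucky split.

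**The allocation may be stratified.** A reader might also infer that allocation ignores these factors. The article gives only the ratio. Stratification factors are commonly left to a full protocol, which is not shown, so no such criticism can be made. If stratification exists, the imbalance probabilities above are too high, but the named tests would still not use the strata.

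**A run-in or a stable-statin rule.** The contrast with the fenofibrate rule tempts one to ask for this. It is a clinical matter and is not argued here.

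**Covariates belong in an analysis plan.** This is partly fair: the article condenses, and it leaves some room in its choice of tests. However, it positively names the tests for the change endpoints, and none of them adjusts.

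**The size is assumed.** This stands. The Discussion does not compare naive with pre-treated patients, and it reports that more than a third did not improve or worsened on high-dose statin. At the low end the gain is under three patients. For LDL, where the Introduction expects a fall of around 60%, a shift of 0.08–0.15 SD is unlikely to matter. The point bears on the imaging and functional endpoints.

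**Conclusion.** The point holds as a matter of precision and robustness. The article allows a heterogeneous baseline, describes a mechanism by which prior statin use would alter the primary imaging endpoints, and then names tests that cannot take it into account.

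Under the assumed 30–50% naive share and 0.4–0.8 SD gap, the cost is about 3–14% of the variance. An unlucky 20-point split, with probability of roughly 7–12% without stratification, would carry a conditional error of about 6–8%. These figures depend entirely on the two assumptions. The text supports neither systematic bias nor a finding against the allocation. Stroke or death is not a change endpoint and is outside this point.

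**What to change.** Make the primary between-arm comparison of each change endpoint a prespecified regression model: linear for continuous endpoints, logistic or ordinal for categorical ones. Adjust each for:
- the baseline value of the outcome;
- days from index event to the baseline assessment;
- statin use at the index event (yes/no);
- index event type (TIA or stroke), for NIHSS, Barthel index, mRS, MoCA and MMSE.

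The named two-sample tests can stay as sensitivity analyses. For plaque enhancement, an ordinal model of the 12-month grade is safer than a logistic model of relief, because a patient at grade 0 cannot fall by a grade.

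Event date and type are already needed for inclusion criterion 2. Statin use is not assured: criterion 5 asks about lipid-lowering therapy only for ages 30–49 and only as one of several alternatives, and section 2.2 lists no medication history. Record statin use at the index event for every patient, at intake or from the chart. Both additions remain possible after enrolment has begun, provided the model is fixed before data by arm are seen.

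The cost is one data item and a few degrees of freedom. No visits, scans or patients are added. With sparse categories, such as new T1 hyperintensity, the covariate list may need to be shortened, and that rule should be fixed in advance too.

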**Figure 1 fig1:**
[figure not shown]
Schematic of the study design and treatment schedule. Statin, including rosuvastatin 10–20 mg or atorvastatin 20–80 mg, will be administered in both arms for 12 months. All patients will receive optimal medical management with aggressive control of the risk factors (e.g., appropriate use of antiplatelet, antihypertensive, and antidiabetic drugs). Patients in the intervention arm will receive an additional treatment of evolocumab 150 mg subcutaneously every 2 weeks for 12 months. All patients will undergo high resolution vessel wall magnetic resonance imaging (HR-vwMRI) at recruitment and after 6 and 12 months. Blood tests will be performed at baseline and at 1, 3, 6, and 12 months after recruitment. Rating scales, including NIHSS, Barthel index, modified Rankin Scale, MoCA, and MMSE, will be used to assess neurological functions and cognitive functions at baseline and at the 3rd, 6th, and 12th months after recruitment.

